### Focus Groups

Two different single-session focus groups (one with patients, one with psychiatrists) will be carried out to discuss the experience with SIDEAL, and to collect suggestions and reports of errors. A maximum of 10 subjects included in the feasibility study will be selected for the focus group.

Personal interviews with some users will also be conducted to collect qualitative information. Data will be analyzed using qualitative methods. Focus group sessions will be transcribed verbatim and analyzed with NVivo 10 or a similar software package. In analyzing the transcripts, areas of consensus and discrepancy will be discussed. Coding and categorizing will follow the principles of inductive content analysis [17]. The information collected will be helpful to improve SIDEAL, a new version of which will be produced if considered necessary.

### Randomized Controlled Trial

The last step will be the completion of a randomized, controlled trial. Selected subjects will be randomized to standard treatment plus SIDEAL or to standard treatment alone. There will be no exclusion criteria with regard to what is considered standard treatment. In this sense, patients may be receiving any treatment, pharmacological or psychosocial, on an individual or group basis. The study will last 24 weeks. The initial hypothesis, based on previous research on the efficacy of alcohol apps, is that the addition of SIDEAL will improve drinking outcomes in alcohol-dependent patients, with especially significant reductions in the number of heavy drinking days and mean alcohol consumption. User acceptance and usability will be essential to achieve this objective. In addition, continuous monitoring and feedback, as well as psychoeducational content and messages, are expected to be effective for decreasing alcohol consumption.

To be included, subjects will be required to have a diagnosis of alcohol dependence or alcohol use disorder according to their psychiatrists, a drinking pattern in the previous 4 weeks consisting of >5 heavy drinking days (HDD; defined as a day with alcohol consumption ≥60 g for men and ≥40 g for women), and an average alcohol consumption above medium risk levels (ie, >40 g of alcohol/day for men and >20 g of alcohol/day for women) in the 4 weeks before study entry. Patients will be evaluated at baseline and week 24. Baseline assessments will be the same as those in the feasibility study, with the addition of the following liver enzyme tests: gamma-glutamyl transferase (GGT), aspartate aminotransferase (AST), and alanine aminotransferase (ALT); and the Addiction Severity Index (ASI) [18]. At week 24, drinking variables (number of HDDs and mean units per day) taken from the TLFB for the previous 6 weeks will be collected. Blood tests and the Addiction Severity Index will be evaluated again.

The statistical analysis will consist of a multivariate regression analysis with change from baseline to study end in number of HDDs and mean alcohol consumption per day as the dependent variables. Age, sex, baseline alcohol drinking, and ASI scores will be entered as independent variables. A secondary analysis will compare changes between groups in ASI scores and liver enzyme levels. A logistic regression analysis will also be conducted with the same independent variables, where rates of point and continuous prevalence of abstinence will be considered as the dependent variables.

For sample size calculation, using a significance level of 5%, and assuming a standard deviation for the change from baseline in number of HDD of 6 days, 45 patients in each treatment group would provide 80% power for detecting a difference between treatment groups of 4 heavy drinking days, assuming a dropout rate of 25% at week 24. Results will be reported according to the CONSORT-EHEALTH checklist [19].

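### Randomised group is missing from the stated predictors of both the linear and the logistic drinking models, so no stated analysis compares the arms on the outcomes that the trial was sized for

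*Protocol article*

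**What the plan says.** All the relevant text is in the Randomized Controlled Trial section of the protocol article.

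- **Design.** "Selected subjects will be randomized to standard treatment plus SIDEAL or to standard treatment alone".
- **Hypothesis.** The section expects that "the addition of SIDEAL will improve drinking outcomes in alcohol-dependent patients", above all HDDs and mean consumption.
- **Main analysis.** A "multivariate regression analysis with change from baseline to study end in number of HDDs and mean alcohol consumption per day as the dependent variables".
- **Predictors.** "Age, sex, baseline alcohol drinking, and ASI scores will be entered as independent variables".
- **Abstinence.** "A logistic regression analysis will also be conducted with the same independent variables", with point and continuous abstinence as the outcomes.
- **Between-group analysis.** "A secondary analysis will compare changes between groups in ASI scores and liver enzyme levels".
- **Sample size.** 45 per group, for 80% power at the 5% level to detect a 4-day difference between groups, with an SD of 6 days for change in HDDs and 25% dropout.
- **ASI timing.** The ASI is added to the baseline assessments, and at week 24 "Blood tests and the Addiction Severity Index will be evaluated again".

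**The concern.** The predictor list is definite. It has no wording such as *including* or *among others*, and the logistic analysis reuses it by reference. Randomised group is not on it. The phrase that does compare groups is attached only to ASI scores and liver enzymes, so no other sentence supplies the missing contrast for the drinking outcomes.

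At stake is the main result of the trial. Run literally, the main analysis would describe which patients change their drinking (by age, sex, baseline drinking and ASI) and would not say whether the app changes it. If an analyst repairs the omission later, the text does not say how. The options include a group coefficient adjusted for the listed covariates, an unadjusted comparison beside a predictor model, and a model with group-by-covariate terms. These are different main analyses, and the choice should not be open once data have been seen.

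**Working it through.** **Step 1. What the sample size is for.** Inputs from the Randomized Controlled Trial section: difference 4 HDDs, SD of change 6, alpha 5%, power 80%, dropout 25%. Sidedness is not stated; two-sided is assumed.

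- Evaluable per arm: n = 2 x [6 x (1.960 + 0.842) / 4]² = 35.3, rounded up to 36.
- Dropout allowance: 36 x 1.25 = 45, which is the stated figure. (36 / 0.75 would be 48; that is a separate matter.)
- One-sided alpha gives 28 evaluable per arm, hence 35 (x 1.25) or 38 (/ 0.75). It does not give 45, so the two-sided reading is the one that fits.

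The 45 per group is therefore a two-group calculation for the between-arm difference in change in HDDs.

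**Step 2. What the stated model contains.** Treating ASI as one term, the linear model for each drinking outcome is

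change = b0 + b1·age + b2·sex + b3·baseline drinking + b4·ASI + error.

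It has five coefficients and none for group. The logistic models have the same five terms on the log-odds scale. The 4-day difference in Step 1 is not a parameter of any stated model.

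**Step 3. Stated analyses against the hypothesis.**

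| Outcome | Stated analysis | Compares the arms? |
|---|---|---|
| Change in HDDs | regression on four covariates | no |
| Change in mean consumption | regression on four covariates | no |
| Point and continuous abstinence | logistic regression, same covariates | no |
| Change in ASI, liver enzymes | secondary comparison | yes |

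The hypothesis concerns drinking. The only row that compares the arms does not.

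**Step 4. Illustration by simulation.** Assumptions: 34 completers per arm (45 x 0.75 = 33.75), normal errors with SD 6, covariates unrelated to outcome, 4,000 runs.

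| Model | True effect -4 HDDs | No effect |
|---|---|---|
| With group | mean estimate -3.97; group term significant in 74% of runs | significant in 4.7% |
| As written | no SIDEAL coefficient; overall F test significant in 5.6% | significant in 5.1% |

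The simulation error of a rate near 5% is √(0.05 x 0.95 / 4,000) = 0.34 percentage points, so 5.6% and 5.1% are not distinguishable. A 4-day benefit leaves no trace in the tests of the model as written. The 74% lies a little below the 77% of a plain t test at 34 per arm because the simulated covariates are pure noise and cost some precision.

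**The case against.** The strongest reply is that the comparison is fixed elsewhere. The sample size is set for a between-group contrast on the regression's own dependent variable, the hypothesis names the addition of SIDEAL, and the Abstract says that consumption is studied to test efficacy. On that reading the list is simply the adjustment set of a two-arm trial with the arm taken for granted. It can be added that this is a condensed article, that a fuller protocol or SAP may name the group term, and that the list does not claim to be exhaustive.

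Much of this stands as evidence of intent: group was very probably meant to be in the models. It does not remove the point. The article is not silent on the predictors. It states a list, reuses it for a second family of models, and reserves its between-group wording for other outcomes. That is a statement in conflict with its surroundings, not a detail left for later.

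Two stronger readings might be inferred, and neither is supported.

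- **That the trial does not aim to compare the arms on drinking.** The hypothesis and the sample size show that it does.
- **That week-24 ASI will be entered as a covariate and absorb part of the treatment effect.** Nothing says so. The word *baseline* before alcohol drinking can be read to cover ASI as well, the ASI is listed among the baseline assessments, and its change is a separate secondary outcome. The documents give no ASI effect, SD or correlation with drinking, so any figure for a loss of effect would be invented. What remains is a small ambiguity, because the ASI is measured twice and the list does not say which value is meant.

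**Conclusion.** The point holds as a fault in the stated models. Randomised group is in neither the linear nor the logistic specification, and no other stated analysis compares the arms on HDDs, mean consumption or abstinence. Taken literally, the number of treatment-effect estimates for these outcomes is zero, while the sample size of 45 per group exists to detect one of them.

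The conclusion rests on the wording of the predictor list and on the absence of any other between-group analysis of drinking in the article. It does not depend on the simulation, whose covariates and error distribution are assumed. It is worth correcting before any outcome data are analysed, because the hypothesis cannot be answered from the models as written. The timing of the ASI covariate is only a brief clarification.

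**What to change.** Replace the predictor sentence with text to this effect:

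> Randomised group (SIDEAL plus standard treatment versus standard treatment alone) is the term of interest in the linear and the logistic models. Age, sex, baseline drinking and the baseline ASI score are covariates. The adjusted group effect with its 95% confidence interval is the estimate of the treatment effect: a difference in mean change for HDDs and daily consumption, and an odds ratio for abstinence.

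Writing *baseline* before ASI settles its timing, which matters because the ASI is repeated at week 24 and its change is an outcome.

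The cost is a sentence or two of analysis text. No extra data or visits are needed, and the stated 45 per group is unaffected because it was already derived for a two-group comparison. If a fuller protocol or SAP already names the group term, it is enough to bring the article's wording into line with it.

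### The ASI and liver-enzyme comparison is specified as a between-group comparison of changes with no baseline covariate named; adjusting each outcome for its own baseline would be modestly more precise at no cost

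*Protocol article*

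**What the plan says.** All of this is in the Protocol article, Randomized Controlled Trial section.

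- **Baseline measurement.** The feasibility-study assessments are repeated "with the addition of the following liver enzyme tests: gamma-glutamyl transferase (GGT), aspartate aminotransferase (AST), and alanine aminotransferase (ALT"), "and the Addiction Severity Index (ASI").
- **Follow-up.** At week 24, "Blood tests and the Addiction Severity Index will be evaluated again".
- **Analysis of these outcomes.** "A secondary analysis will compare changes between groups in ASI scores and liver enzyme levels". No test, model or covariate is given.
- **Analysis of drinking outcomes.** The dependent variables of the main regression are the changes in heavy drinking days and in mean daily consumption. For that model, "Age, sex, baseline alcohol drinking, and ASI scores will be entered as independent variables".
- **Analysis of abstinence.** "A logistic regression analysis will also be conducted with the same independent variables".

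The ASI and enzyme comparison is therefore the only one of the three RCT analyses without a stated covariate set.

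**The concern.** Each secondary outcome has a baseline value, and that value usually predicts the week-24 value. Leaving it out of the model, and relying on subtraction alone, fixes the baseline slope at 1 instead of letting the data estimate it. When the true slope is below 1 this has two effects. The estimate carries more noise than it needs to, and a chance difference between the arms at baseline pushes the estimated effect in the opposite direction.

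The stake is the precision of the secondary results. The drinking outcomes come from self-report on the Timeline Follow-Back, and the Discussion concedes that participants cannot practicably be blinded. The enzymes are the only laboratory outcomes listed, so a reader may well look to them for corroboration. The article does not itself assign them that role, and the argument does not extend to the ASI.

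**Working it through.** The plan states no figure for the ASI or enzyme analysis, so there is none to reproduce. The check has three parts.

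**1. What the text fixes.** The ASI and enzyme sentence neither states nor excludes baseline adjustment. Its neighbours both state their covariates, so the unadjusted reading is the natural one. Suppose instead that the main regression's covariates were meant to carry over. The ASI might then be adjusted for its own baseline, if the ASI scores in that list are the baseline ones. The enzymes would not be, because the list contains no baseline GGT, AST or ALT.

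**2. Precision.** Inputs: a common standard deviation s at both visits and a baseline to week-24 correlation r. Neither is in the article, so both are assumptions, and r is shown over 0.3 to 0.9.

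- Variance per patient of an unadjusted change: 2(1-r)s².
- Residual variance per patient after adjustment for baseline: (1-r²)s².
- Ratio: (1-r²) / [2(1-r)] = (1+r)/2. The standard error ratio is its square root.

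| r (assumed) | Change, in s² | Adjusted, in s² | Variance ratio | SE ratio | Fall in SE |
|---|---|---|---|---|---|
| 0.3 | 1.40 | 0.91 | 0.65 | 0.806 | 19% |
| 0.5 | 1.00 | 0.75 | 0.75 | 0.866 | 13% |
| 0.7 | 0.60 | 0.51 | 0.85 | 0.922 | 8% |
| 0.8 | 0.40 | 0.36 | 0.90 | 0.949 | 5% |
| 0.9 | 0.20 | 0.19 | 0.95 | 0.975 | 2.5% |

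Adjustment spends one degree of freedom, which the table ignores.

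**3. Chance imbalance.** Inputs: 45 patients per group and 25% dropout, both from the sample size paragraph. Evaluable patients per arm: 45 × 0.75 = 33.75, about 34.

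- Standard error of the chance baseline difference D: √(2/34) = 0.24 SD.
- Given D, the expected week-24 difference is the treatment effect plus rD. Subtracting D leaves the treatment effect minus (1-r)D.
- At r = 0.5 and an imbalance of one standard error, the shift is -(1-0.5) × 0.24 = -0.12 SD.
- At r = 0.9 it is -(1-0.9) × 0.24 = -0.024 SD.

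Under randomisation D averages zero, so there is no systematic bias. The shift belongs to the single trial that is reported.

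**Equivalence of the two adjusted forms.** If change = a + b·group + g·baseline, then adding baseline to both sides gives week-24 value = a + b·group + (g+1)·baseline. The treatment coefficient b and its standard error are the same in both.

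**The case against.** The strongest objection is that the defect is read into silence. The article does not call the comparison raw or unadjusted. It pairs change as the dependent variable with a baseline covariate in its own drinking regression, so speaking of changes does not rule adjustment out. A journal article may also leave the model for secondary outcomes to the full protocol or the analysis plan. This stands in part: a reader might infer that the plan commits to an unadjusted analysis, and the text does not establish that. What remains is that the article does state a method for these outcomes, gives covariates for the analyses on either side, and has a covariate list without the enzyme baselines.

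Three further readings are tempting and go too far.

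- **That chance imbalance is left uncorrected.** A change score subtracts the whole baseline. When r is below 1 its fault is over-correction, by (1-r) times the imbalance, and it remains unbiased on average.
- **That the loss amounts to many patients.** The trial is sized on heavy drinking days; no sample size or power statement depends on ASI or enzymes. On the standard error scale the gain is modest, and it is small if r is high.
- **That raw enzyme changes will be dominated by a few extreme values.** The article gives no enzyme distribution, so skewness cannot be asserted from it. Strong skewness would also sit poorly with the equal-variance assumption behind the ratio.

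**Conclusion.** The point holds as a modest improvement to the analysis of secondary outcomes. As written, the ASI and enzyme comparison uses changes and names no baseline covariate, although each baseline is collected. If it is carried out unadjusted, the standard error is larger than it need be: adjustment would lower it by about 8% to 19% for r between 0.7 and 0.3, and by 2.5% to 5% for r between 0.9 and 0.8. These figures rest on equal variances at the two visits and on an assumed r. The direction does not depend on the exact r: under equal variances (1+r)/2 is below 1 for any r below 1, apart from the degree of freedom spent. The main drinking analysis, which is already adjusted for baseline drinking, and the stated sample size are untouched.

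**What to change.** Add one sentence to the statistical analysis paragraph: each ASI and liver-enzyme comparison will be a regression of the change (or, equivalently, the week-24 value) on treatment group plus that outcome's own baseline value, reported as an adjusted difference with its 95% confidence interval. The present wording about changes can stay.

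A log scale for GGT, AST and ALT is an optional choice if those values prove skewed; if it is wanted, it is best fixed before the data are seen. On that scale the baseline covariate would be logged too, and the result reported as a ratio of geometric means.

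The cost is wording only: every value needed is already collected, and no visit, test or patient is added.

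### With 25% dropout, 45 patients per group give about 77–78% power for a 4-day difference, not the stated 80% (two-sided, unadjusted comparison)

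*Protocol article*

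**What the plan says.** The Randomized Controlled Trial section of the Protocol article justifies the trial's size in one sentence. It sets a 5% significance level and takes the variability as "assuming a standard deviation for the change from baseline in number of HDD of 6 days". It then states that "45 patients in each treatment group would provide 80% power for detecting a difference between treatment groups of 4 heavy drinking days". The same sentence closes with its allowance for loss to follow-up, which reads "assuming a dropout rate of 25% at week 24".

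The sentence does not give the test, whether it is one- or two-sided, the number of completers required, or how dropout was allowed for. It claims no variance reduction from covariates. The paragraph before it plans a regression of change from baseline, with age, sex, baseline drinking and ASI scores as independent variables.

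**The concern.** Every quantity needed to check the claim is printed, so the check does not depend on details that an article leaves to a fuller document. A dropout allowance should leave enough completers for the intended power after the assumed loss. Here the number left is below the number required, under the plan's own assumptions.

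This sentence is the only quantitative basis for the size of the efficacy trial, and 25% is the planners' own expected dropout. Readers will judge the result, especially a null one, against the stated 80%.

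**Working it through.** **Inputs**, all from the sample size sentence: difference δ = 4 heavy drinking days, SD of change σ = 6, significance 5%, power 80%, 45 per group, dropout 25%. **Assumed, because not stated:** a two-sided test and an unadjusted comparison of two means.

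**1. Completers needed per group.** Normal formula: n = 2(1.960 + 0.842)² σ²/δ² = 2 × 7.85 × 36/16 = 35.3, rounded up to 36. The t test gives 36.3, rounded up to 37.

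**2. Trying to reproduce 45.**

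| Route | Per group |
|---|---|
| Normal, divided by (1 − 0.25): 36 / 0.75 | 48 |
| Normal, unrounded: 35.3 / 0.75 | 47.1 |
| t test, divided by (1 − 0.25): 37 / 0.75 = 49.3 | 50 |
| Normal, multiplied by (1 + 0.25): 36 × 1.25 | 45 |
| t test, multiplied by (1 + 0.25): 37 × 1.25 = 46.25 | 47 |

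Only 36 × 1.25 gives 45. Multiplying by 1.25 does not offset a 25% loss, because 1.25 × 0.75 = 0.9375, and 36 × 0.9375 = 33.75.

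**3. Power of the stated design.** Completers are 45 × 0.75 = 33.75 per group.
- Standard error = 6 × √(2/33.75) = 1.461, and 4/1.461 = 2.739.
- Normal: Φ(2.739 − 1.960) = Φ(0.779) = 78.2%.
- Noncentral t: 77.0%. In whole patients it is 76.0% with 33 per group, 76.7% with 33 and 34, and 77.3% with 34 per group.

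**4. Difference detectable at 80% power.** Normal: (1.960 + 0.842) × 1.461 = 4.09 days. By t: 4.15 days.

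**5. Dropout at which 45 per group keeps 80%.**
- t test, 37 completers: 1 − 37/45 = 17.8%.
- Normal, 36 completers: 1 − 36/45 = 20%.
- Normal, unrounded 35.3: 1 − 35.3/45 = 21.5%.

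The limit is therefore roughly 18% to 21%.

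**6. Other readings of the sentence.**
- *45 are completers:* power would be 88.5% (normal) or 87.9% (t), not 80%.
- *One-sided 5%:* 28 completers are needed, so 28/0.75 = 37.3, rounded up to 38 (35 if multiplied by 1.25). Neither is 45. One-sided power at 33.75 completers is about 86%.

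**7. Power with 48 per group.** The 36 completers left give 80.7% (normal) or 79.7% (t), so 48 is sufficient by the normal formula and marginally short by t.

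**The case against.** The strongest reply is that the gap is trivial. By the normal formula, which is the one that yields 36, power is only 1.8 points below 80%. The detectable difference moves by about a tenth of a day. The SD of 6 is a round planning value, and 5.87 (normal) or 5.78 (t) would restore 80%. This stands as an argument about severity: the point is minor. It does not make the printed combination consistent.

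The planned analysis is also not the unadjusted comparison used here. If the covariates have a correlation r with the change score, the residual SD is about 6√(1 − r²). Power then reaches 80% at r of about 0.21 (normal) or 0.27 (t). Such correlations are modest, so the analysis actually planned may well reach 80%. This also stands. A reader might infer that the trial could never have 80% power, and the document does not support that. Equally, the sample size sentence uses the SD of the raw change and invokes no adjustment, so the possible gain does not repair it.

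A reader might further take it as fact that dropout was added by multiplying by 1.25. The exact match makes that likely, but the article shows no formula or intermediate number. The shortfall holds whatever produced 45.

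Finally, a one-sided 5% test would give power above 80%. The article does not state one, and a one-sided calculation does not lead to 45.

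**Conclusion.** The sentence is wrong as written, and the correction is minor. Under a two-sided, unadjusted comparison with the plan's own inputs, 45 per group with 25% dropout leaves about 34 completers where 36 (normal) or 37 (t) are needed. The power is about 77–78%. The shortfall is 3 enrolled patients per group by the normal formula (48 − 45) or 5 by t (50 − 45).

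The conclusion rests on the two-sided assumption and on no variance reduction from covariates. It does not show that the trial is materially underpowered, and it gives no reason by itself to change enrolment.

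**What to change.** Restate the sentence and leave enrolment as it is, for example: *45 patients per group with 25% dropout (about 34 evaluable per group) give about 77–78% power for a difference of 4 heavy drinking days (SD of change 6, two-sided 5%, unadjusted comparison); 80% power requires dropout of no more than roughly 18% (t test) to 21% (normal approximation).*

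If the sponsor prefers to keep 80% power together with 25% dropout, the matching number is 48 per group (normal) or 50 (t), that is 96 or 100 in total against 90. If the sponsor wishes to rely on covariate adjustment, the assumed correlation should be stated with the calculation.

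The restatement costs one sentence and a slightly less favourable power figure, with no extra patients.
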